### Sample size

The sample size was calculated to test the superiority of a BIA-guided precision fluid management strategy over standard empirical diuretic therapy. Based on previous data, the 3-month incidence of the composite outcome of heart failure rehospitalization or all-cause mortality in the control group was assumed to be 24.9% (1). We hypothesized a 20% relative risk reduction with the intervention, corresponding to an expected event rate of 19.9% in the intervention group.

With a significance level of 0.05, a power of 80%, and a 1:1 randomization ratio, a total of 242 participants per group were required. Allowing for a 10% attrition rate, the final target sample size was increased to 269 participants per group, yielding a total sample size of 538. Sample size calculations will be performed using PASS software.

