### Study outcomes and measurement

The primary outcome will be assessed at three predefined time points: 2 weeks, 4 weeks, and 12 weeks after discharge. Secondary clinical endpoints will be evaluated at the same time points as the primary outcome. Patient-reported quality of life measures will be assessed during hospitalization, at discharge, and at 12 weeks post-discharge. Additionally, assessments of symptom relief and safety monitoring will be conducted during the hospital stay (as detailed in Table 2).

**Table 2 T2:** Summarizes the timing of enrollment, interventions, and outcome assessments.

Visit ID	V1	V2	V3	V4	V5	V6
Case Report Form (CRF)	A	B		C	D	E
	Screening	Baseline/Randomization	Discharge	Follow-up 1	Follow-up 2	End-of-Study Visit
Time from Randomization	-1-0 week	-1-0 week	0 week	2 week	4 week	12 week
Assessment Window	–	–		±3 days	±3 days	±3 days
Informed Consent	X					
Demographic Data		X				
Personal History		X				
Physical Examination		X				
Comorbidities		X				
Laboratory Tests		X				X
Concomitant Medications		X		X	X	X
Event Adjudication				X	X	X
Heart Failure Symptom Assessment (KCCQ/VAS)		X	X			X (KCCQ)
Bioelectrical Impedance Measurement		X (Daily during hospitalization, intervention group)				

The primary outcome of this study is the composite endpoint of heart failure rehospitalization and all-cause death within 3 months after discharge; the secondary outcomes include rehospitalization for heart failure within 3 months after discharge, cardiovascular death within 3 months after discharge, all-cause death within 3 months after discharge, the change of Kansas City Cardiomyopathy Questionnaire (KCCQ) quality of life score from baseline to discharge and 3 months after discharge, the dose of diuretics used during hospitalization and dyspnea and changes in overall condition at 72 h after admission (VAS scale); the safety endpoints include the incidence of acute kidney injury and hypotension during hospitalization, the incidence of electrolyte imbalance during hospitalization and follow-up period.

The time origin for the primary endpoint is defined as the date of hospital discharge. Participants will be followed for 90 days after discharge.

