### Statistical analysis

Analyses will be performed with SPSS 26.0 (SPSS Inc., Chicago, IL) and R 4.2.1 (R Foundation, Vienna). All analyses will follow the intention-to-treat principle, with participants analyzed according to the randomized assignment. Baseline characteristics will be summarized using mean (SD) or median (IQR) for continuous variables and counts (%) for categorical variables.

The primary endpoint (time to first occurrence of heart-failure rehospitalization or all-cause death within 3 months) will be analyzed using Kaplan–Meier methods and compared between groups using the log-rank test. Treatment effect will be estimated using Cox proportional-hazards models, reporting hazard ratios (HRs) with 95% confidence intervals. The proportional-hazards assumption will be assessed using Schoenfeld residuals. A prespecified adjusted Cox model will include clinically relevant baseline covariates (e.g., age, sex, BMI, LVEF, NYHA class, baseline NT-proBNP). Baseline diuretic dose (expressed as furosemide-equivalent dose) will be compared between groups and included as a covariate in adjusted analyses if clinically relevant imbalance is observed.

For time to first heart-failure rehospitalization, death will be treated as a competing event; Fine–Gray subdistribution hazard models will be used as a supportive analysis. Cardiovascular and all-cause mortality will be analyzed using KM/log-rank and Cox models as appropriate.

The total number of heart-failure rehospitalizations within 3 months will be analyzed using a negative binomial regression model (offset by follow-up time), reporting incidence rate ratios (IRRs) with 95% CIs. As a sensitivity analysis, a recurrent-event time-to-event model (e.g., Andersen–Gill) may be applied. Deaths occurring during the index hospitalization will be recorded as safety outcomes but will not be included in the primary time-to-event analysis, which focused on post-discharge events.

Changes in weight, NT-proBNP, and KCCQ scores over time will be evaluated using linear mixed-effects models with random participant intercepts, incorporating all available repeated measurements.

Safety endpoints (acute kidney injury, hypotension, electrolyte imbalance) will be summarized as counts (%) and compared using *χ*² or Fisher's exact tests.

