The primary endpoint will be tested at a two-sided alpha level of 0.05. All secondary endpoints will be analyzed as exploratory; no formal multiplicity adjustment will be applied. For secondary and safety outcomes, effect estimates with 95% confidence intervals will be reported and interpreted cautiously.

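### Cardiovascular mortality is assigned Kaplan-Meier with no competing-event method, so its descriptive 90-day risk would be slightly overstated

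*Protocol article*

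**What the plan says.** Study outcomes and measurement lists two mortality outcomes among the secondary endpoints: "cardiovascular death within 3 months after discharge, all-cause death within 3 months after discharge". On duration, the same section states: "Participants will be followed for 90 days after discharge".

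Statistical analysis gives both outcomes one set of methods: "Cardiovascular and all-cause mortality will be analyzed using KM/log-rank and Cox models as appropriate". The sentence just before handles the other component of the composite differently: "For time to first heart-failure rehospitalization, death will be treated as a competing event; Fine–Gray subdistribution hazard models will be used as a supportive analysis".

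On the weight of these results, the plan says: "All secondary endpoints will be analyzed as exploratory; no formal multiplicity adjustment will be applied". It promises effect estimates with 95% confidence intervals for secondary outcomes.

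**The concern.** The two mortality outcomes differ in structure. Nothing can prevent all-cause death from being observed except the end of follow-up or loss to follow-up, so Kaplan-Meier estimates its risk correctly. A patient who dies of a non-cardiovascular cause, however, can no longer die of a cardiovascular one. Standard Kaplan-Meier for cardiovascular death removes that patient from the risk set as if the cardiovascular death might still come later. One minus Kaplan-Meier then describes a hypothetical population in which nobody dies of other causes. The listed outcome is cardiovascular death that actually occurs within 3 months, and its risk is the cumulative incidence.

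The plan applies the competing-event idea to one cause-specific endpoint and not to the next. At stake is the cardiovascular mortality percentage reported for each arm, which would be biased upward. The questions to settle are how large that bias is and whether it reaches the comparison between arms.

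**Working it through.** The plan states no figure for cardiovascular or non-cardiovascular mortality, so there is nothing of its own to reproduce here. The check compares the named estimator with the cumulative incidence.

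**Inputs**
- Horizon: 90 days from discharge (Study outcomes and measurement).
- Arm size: 269, the target after attrition (Sample size), used only to express the result in patients.
- All-cause 90-day mortality M: not given. Assumed 5%, 10%, 15%.
- Non-cardiovascular share of deaths s: not given. Assumed 20%, 30%, 40%.
- Proportional cause-specific hazards and no other censoring: assumed.

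**Formulas**
- Total cumulative hazard: H = -ln(1 - M).
- One minus Kaplan-Meier for cardiovascular death: 1 - exp(-(1 - s)H) = 1 - (1 - M)^(1 - s).
- Cumulative incidence of cardiovascular death: (1 - s)M.

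Example, M = 15% and s = 40%: 1 - 0.85^0.6 = 9.29%, against 0.6 × 15% = 9.00%.

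| M | s | 1 - KM | Cumulative incidence | Excess (points) | Relative | Patients per 269 |
|---|---|---|---|---|---|---|
| 5% | 20% | 4.02% | 4.00% | 0.02 | 0.5% | 0.05 |
| 5% | 40% | 3.03% | 3.00% | 0.03 | 1.0% | 0.08 |
| 10% | 20% | 8.08% | 8.00% | 0.08 | 1.0% | 0.22 |
| 10% | 30% | 7.11% | 7.00% | 0.11 | 1.6% | 0.30 |
| 10% | 40% | 6.13% | 6.00% | 0.13 | 2.1% | 0.34 |
| 15% | 20% | 12.19% | 12.00% | 0.19 | 1.6% | 0.52 |
| 15% | 40% | 9.29% | 9.00% | 0.29 | 3.2% | 0.78 |

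**Stress case.** Sample size says that the 3-month composite rate "in the control group was assumed to be 24.9" per cent. If every one of those events were a death and s were 40%, the figures would be 15.79% against 14.94%, an excess of 0.85 points. This is deliberately unrealistic, because the composite also counts rehospitalisations.

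**Against sampling error.** At the worst assumed case the binomial standard error for one arm is sqrt(0.09 × 0.91 / 269) = 1.7 points, so the excess of 0.29 is about one sixth of a standard error.

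**Between arms.** If both arms lie within the assumed ranges, the difference in reported risk is distorted by at most 0.29 - 0.02 = 0.27 points, even if their non-cardiovascular mortality differs.

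**Test and hazard ratio.** The log-rank test was simulated with 269 per arm and 4,000 runs. Cardiovascular hazards were equal in the two arms, and the non-cardiovascular hazard differed threefold between them. The two-sided 5% test rejected in 5.0% of runs, so its size was kept. In the arm with more non-cardiovascular deaths, one minus Kaplan-Meier averaged 8.10% against a cumulative incidence of 7.97%, in line with the table.

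**The case against.** The strongest case against raising this is that the plan never writes that non-cardiovascular deaths are censored. It also never says that one minus Kaplan-Meier will be the reported cardiovascular risk. The phrase about using the models as appropriate leaves discretion, and an analysis plan that is not shown may settle the matter. The first part is right: the censoring is implied, not stated. The discretion does not close the gap, though, because every listed option (Kaplan-Meier, log-rank, Cox) censors non-cardiovascular death when the event is cardiovascular death, and no cumulative-incidence estimator is among them. The point therefore concerns a method that the text names, not a detail that it omits.

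The second objection is that the effect is immaterial on an exploratory endpoint. That stands, and it is why the point is minor. The assumed shares are also unsupported by the text. Table 1 excludes patients with other serious diseases threatening survival within 3 months, severe renal insufficiency or decompensated cirrhosis, which may make the non-cardiovascular share lower than assumed.

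Several stronger readings are tempting, and the document does not support them:
- **The section contradicts itself.** For heart-failure rehospitalisation, Fine-Gray is only supportive. The contrast with cardiovascular death is an uneven application of one idea, not a contradiction.
- **The treatment comparison is biased.** The log-rank test and Cox hazard ratio are valid for the cause-specific hazard.
- **Over-diuresis would drive the arms apart in non-cardiovascular deaths.** The Introduction mentions electrolyte disturbance, hypotension, worsening renal function and clinical deterioration. It says nothing about non-cardiovascular death.
- **The cause-specific curves will visibly exceed the all-cause curve when added.** No non-cardiovascular curve is planned.

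**Conclusion.** The point holds as a small improvement. The plan names an estimator for cardiovascular mortality that, used in the standard way, overstates the 90-day risk whenever non-cardiovascular deaths precede later cardiovascular ones. The excess is about 0.02-0.29 percentage points (0.5%-3.2% relative). That range rests on assumed all-cause mortality of 5%-15%, an assumed non-cardiovascular share of 20%-40%, proportional cause-specific hazards and no other censoring.

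A reader might infer that the reported cardiovascular mortality will be materially wrong. The figures do not support that: the direction is certain once such deaths occur, but the size is well inside sampling error and no conclusion of the trial would turn on it. The primary endpoint and all-cause mortality are untouched.

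**What to change.** Replace the shared sentence in Statistical analysis with wording to this effect: all-cause mortality is analysed by Kaplan-Meier, log-rank and Cox; cardiovascular mortality is reported as the Aalen-Johansen cumulative incidence by arm with non-cardiovascular death as the competing event, with the log-rank test and the Cox hazard ratio retained and labelled as cause-specific.

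The cost is one sentence. Under Event ascertainment and adjudication, blinded adjudicators already determine both cardiovascular and all-cause mortality at 3 months, so the competing event follows by subtraction. R is already planned and can produce the estimate. No new data, visits or change in sample size are needed.

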## Introduction

Acute heart failure (AHF) is a clinical syndrome with rapid onset or sudden worsening of heart failure symptoms and signs, triggered by diverse etiologies. It is characterized by elevated plasma natriuretic peptides and often follows a life-threatening course that requires prompt medical intervention, frequently necessitating emergency hospitalization. Acute decompensation of chronic heart failure represents the predominant AHF phenotype, accounting for approximately 70%–80% of all AHF admissions, and is associated with poor prognosis. Registry data indicate that in-hospital mortality for AHF is approximately 12%, while the incidence of death or heart failure rehospitalization reaches 30%–45% within 90 days and 67% within one year (1). This high rate of readmissions places a substantial burden on global healthcare resources and leads to critical shortages in hospital bed capacity. Consequently, reducing potentially preventable readmissions has become a key priority for public health policy and hospital quality improvement programs worldwide.

This excess risk has been attributed to inadequate diuresis during index admission; over 50%–70% of patients are discharged with residual fluid overload (2–4). Conversely, intensified inpatient diuretic regimens attenuate congestion at discharge and improve post-discharge outcomes (3). Nevertheless, diuretic use and dose titration in AHF remain a double-edged sword. Early, aggressive diuresis rapidly relieves symptoms, shortens length of stay, and may reduce mortality (5). Conversely, the absence of precise guidance predisposes to over-diuresis, precipitating electrolyte disturbances, hypotension, and worsening renal function with resultant clinical deterioration (6, 7).

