### Study design

This investigator-initiated, single-center, two-arm, randomized controlled trial will be conducted at a tertiary hospital in Xinjiang, China to compare the incidence of composite endpoint events (heart failure rehospitalization and all-cause mortality) between the two groups over a 3-month follow-up period, thereby providing practical evidence to support the clinical application of this technology in this patient population.

A total of 538 adult patients clinically diagnosed with acute decompensation of chronic heart failure and who meet the inclusion and exclusion criteria. The intervention will be conducted during the patients’ hospitalization, and clinical assessments will be performed at 2 weeks, 4 weeks, and 12 weeks after discharge. Figure 1 shows the patient flow through the study. This study is registered at Chinese Clinical Trial Registry (ChiCTR2500111518).

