### Interventions

#### Run-in phase

Instrumentation: Ensure that the Body Composition Monitor (BCM, Fresenius, Germany) used for the measurement and assessment of fluid overload is properly calibrated and maintained in optimal working condition.Staff training: All healthcare personnel participating in the study will receive standardized training to ensure a thorough understanding of the study objectives, methodology, and procedures, as well as the correct use of the measurement devices and the proper interpretation of their results.Patient screening and enrolment: All participants must meet the predefined inclusion and exclusion criteria, and written informed consent must be obtained prior to enrollment. Participants will be informed of the measurement procedures and any lifestyle modifications or treatment regimens required during the intervention period. Randomization will be completed within 24 h of hospital admission.

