#### Control strategy

BCM will not be used; physicians will estimate dry-weight from intake/output records, daily weight, clinical signs, and routine laboratory data to guide diuretic titration, and discharge timing will be determined at the clinician's discretion.

To minimize contamination between study groups, BCM measurements will be performed exclusively in the intervention group by independent research personnel who are not involved in routine clinical care. Participants in the control group do not undergo BCM measurement at any time during hospitalization. BCM results will not be entered into the electronic medical record and will not accessible to treating physicians caring for control-group participants.

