#### Endpoint definitions

Heart-failure rehospitalization is defined as an unplanned hospital admission lasting ≥24 h with a primary diagnosis of heart failure, accompanied by worsening signs/symptoms of congestion and requiring intensification of HF therapy (e.g., intravenous loop diuretics and/or vasoactive therapy). Planned admissions for elective procedures without clinical deterioration are not counted as endpoint events. All-cause death is defined as death from any cause occurring within 90 days after discharge.

Hypotension is defined as a systolic blood pressure <85 mmHg during hospitalization requiring reduction in diuretic therapy or initiation of vasopressor support.

Acute kidney injury (AKI) is defined as the occurrence of any one of the following: 1) Serum creatinine increases by ≥0.3 mg/dl (≥26.5 μmol/L) within 48 h; 2) Creatinine rises to >1.5 times baseline, indicating known or presumed renal dysfunction occurring within 7 days; 3) Urine output <0.5 ml/(kg·h) for at least 6 consecutive hours.

Electrolyte disturbances: 1) Hyperkalemia is defined as any serum potassium level >5.5 mmol/L observed during hospitalization or follow-up. 2) Hypokalemia is defined as any serum potassium level <3.5 mmol/L observed during hospitalization or follow-up. 3) Hyponatremia is defined as any serum sodium level <130 mmol/L observed during hospitalization or follow-up. Hypernatremia is defined as any serum sodium level >150 mmol/L observed during hospitalization or follow-up.

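### The primary analysis starts at discharge and leaves out index-stay deaths, although randomisation and treatment come earlier, so it compares selected survivors and is not intention-to-treat

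*Protocol article*

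**What the plan says.** The order of events is explicit in the protocol article.

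- Run-in phase: "Randomization will be completed within 24 h of hospital admission".
- Study design: "The intervention will be conducted during the patients’ hospitalization".
- Study outcomes and measurement: "The time origin for the primary endpoint is defined as the date of hospital discharge".
- Endpoint definitions: "All-cause death is defined as death from any cause occurring within 90 days after discharge". The secondary outcomes of cardiovascular and all-cause death are likewise limited to the 3 months after discharge.
- Statistical analysis: "Deaths occurring during the index hospitalization will be recorded as safety outcomes but will not be included in the primary time-to-event analysis". The same section opens with "All analyses will follow the intention-to-treat principle, with participants analyzed according to the randomized assignment".
- Control strategy: "discharge timing will be determined at the clinician's discretion".

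The safety endpoints listed under Study outcomes and measurement, and the safety comparisons named under Statistical analysis, are acute kidney injury, hypotension and electrolyte imbalance. Neither list contains death. The paragraph on alpha and multiplicity that closes the Statistical analysis section promises effect estimates with 95% confidence intervals for secondary and safety outcomes.

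**The concern.** A patient who dies before discharge has no time origin, so that patient cannot enter the primary analysis, although randomised and treated. Being discharged alive is a consequence of care after randomisation, and that care is what the trial varies. Conditioning on it breaks the balance that randomisation provided: if the strategies differ in whom they keep alive to discharge, the two discharged groups differ in prognosis before follow-up starts. The date on which the clock starts is also set after randomisation, by clinicians who know the allocation. Blinded adjudication of later events cannot repair either problem.

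At stake is the meaning of the primary result. Deaths during the period in which the intervention is actually delivered play no part in it. A strategy that costs lives in hospital could look better after discharge, and one that saves frail patients could look worse.

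**Working it through.** **Number of patients affected.** The target of 538 comes from the Sample size section. The only in-hospital mortality figure is in the Introduction, "in-hospital mortality for AHF is approximately 12" per cent, from registry data on acute heart failure in general. The values 2% and 5% are assumptions for a younger, selected population.

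- 2%: 538 × 0.02 = 10.8, about 11 patients
- 5%: 538 × 0.05 = 26.9, about 27 patients
- 12%: 538 × 0.12 = 64.6, about 65 patients

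**Can the sign of the effect change?** Let h be control in-hospital mortality and 24.9% the control rate after discharge (the Sample size assumption). Let d be the change in in-hospital mortality caused by the intervention, and r the post-discharge risk that the affected patients have, or would have had. Assume no other treatment effect.

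- Control, all randomised: h + (1 − h) × 0.249
- Intervention, after discharge: [(1 − h) × 0.249 − d × r] / (1 − h − d)
- Intervention, all randomised: h + d + (1 − h) × 0.249 − d × r

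Take h = 12%, with r = 60% (assumed). The control total is 0.12 + 0.88 × 0.249 = 0.339.

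- d = +2 points: after discharge (0.2191 − 0.012)/0.86 = 0.241; all randomised 0.14 + 0.2071 = 0.347
- d = −2 points: after discharge (0.2191 + 0.012)/0.90 = 0.257; all randomised 0.10 + 0.2311 = 0.331

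The same formulas at the lower assumed mortalities, with r = 60%:

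| h | d | After discharge, intervention vs control | All randomised, intervention vs control |
|---|---|---|---|
| 12% | +2 | 24.1% vs 24.9% | 34.7% vs 33.9% |
| 12% | −2 | 25.7% vs 24.9% | 33.1% vs 33.9% |
| 5% | +2 | 24.1% vs 24.9% | 29.5% vs 28.7% |
| 5% | −2 | 25.6% vs 24.9% | 27.9% vs 28.7% |
| 2% | +2 | 24.2% vs 24.9% | 27.2% vs 26.4% |
| 2% | −2 | 25.6% vs 24.9% | 25.6% vs 26.4% |

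In every row the primary analysis points the opposite way from the all-randomised result, each by less than 1 point.

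**Range for the assumed 60%.** From the formulas, the sign reverses for any r above 24.9% and below 100%. At h = 12% and d = +2:

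- r = 40%: 24.5% after discharge, 35.1% overall
- r = 80%: 23.6% after discharge, 34.3% overall
- r = 24.9%: the primary analysis shows no difference, while the all-randomised result is 35.4% against 33.9%

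**Effect of counting these deaths on the planned contrast.** Take equal in-hospital mortality in both arms and the planned 24.9% against 19.9% after discharge, a 20% relative reduction. Each all-randomised rate is h + (1 − h) × the post-discharge rate. The last column is from the pooled two-proportion formula (two-sided 0.05, 80% power).

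| h | All-randomised rates | Relative reduction | Per arm |
|---|---|---|---|
| none counted | 24.9% vs 19.9% | 20% | 1,091 |
| 2% | 26.4% vs 21.5% | 0.0490/0.2640 = 19% | 1,190 |
| 5% | 28.7% vs 23.9% | 0.0475/0.2866 = 17% | 1,347 |
| 12% | 33.9% vs 29.5% | 0.0440/0.3391 = 13% | 1,755 |

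The first row does not reproduce the stated 242 per group. That is a separate problem, and the present point does not rest on it.

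**The case against.** The discharge anchor is deliberate and disclosed. It runs consistently through the abstract, objectives, endpoint definitions and analysis, and it matches the post-discharge vulnerable phase that motivates the trial. The protocol glosses intention-to-treat as analysis by randomised assignment, which it does for everyone who reaches the time origin. Index-stay deaths are not hidden: they are designated safety outcomes, estimates with intervals are promised for safety outcomes, and serious adverse events are monitored. Part of this stands. A reader might infer that in-hospital deaths go unreported, and that would be wrong. What remains is an inconsistency, since the sentence that makes death a safety outcome is not matched by either safety list. Keeping the assigned label on survivors also does not restore the patients left out.

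Three stronger readings go beyond the documents.

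- A reader might infer that the plan is tilted towards a harmful strategy. Nothing shows that the strategy causes in-hospital deaths, and the distortion works equally in the other direction.
- A reader might infer that about 65 patients will be lost and that the analysed number will fall below the 484 required before attrition. The 12% describes acute heart failure generally, whereas this trial limits age to 18 to 75 and excludes severe renal insufficiency and other life-threatening disease. The shortfall needs in-hospital mortality above 1 − 484/538 = 10%.
- A reader might infer that the 10% attrition allowance ignores these deaths. The Sample size section does not define attrition, so this cannot be shown either way.

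**Conclusion.** The point holds as a design flaw that should be corrected. The primary analysis conditions on survival to discharge, which follows both randomisation and the whole intervention, so it is not the intention-to-treat analysis that the protocol says it is. This rests on the text alone and on no assumed figure.

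The size is uncertain because in-hospital mortality in this population is not given: about 11 to 27 patients at an assumed 2% to 5%, and about 65 at 12% as an upper illustration. The sign-reversal calculation shows what is possible, not what is likely. It assumes a 2-point change in in-hospital death and a 60% later risk in the patients concerned, and the discrepancies are about 0.8 points each way, or roughly 2 patients in an arm of 269. The direction cannot be predicted.

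**What to change.** Amend Study outcomes and measurement, Endpoint definitions and Statistical analysis, with the registry entry, before any unblinded look at the data.

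- Include all randomised patients in the primary analysis and count death from any cause from randomisation, index stay included, together with first heart failure rehospitalisation after index discharge.
- Choose one clock. Either start time at randomisation with a fixed horizon, or keep the discharge clock and count an index-stay death as a day-0 event, confirming that the software retains such records. The second option keeps 90 days of post-discharge follow-up for every survivor.
- Keep the discharge-anchored analysis as supportive.
- Extend the all-cause and cardiovascular death endpoints to the index stay, and add in-hospital death to the safety endpoints and safety comparisons.

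No new data are needed, because these deaths are already to be recorded. The costs are real, however. The composite no longer describes only the post-discharge phase. In-hospital deaths that treatment does not affect dilute the relative effect, so the assumed event rates and the stated power must be restated; on the planned rates the reduction falls from 20% to between 19% and 13% over the mortality range above. With a fixed horizon from randomisation, time at risk of rehospitalisation depends on length of stay, which the strategy may alter. With the day-0 option, survivors' clocks still start on a date chosen by unblinded clinicians.

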#### Event ascertainment and adjudication

Potential endpoint events will be identified through 1) in-hospital electronic medical records and discharge databases, and 2) standardized follow-up contacts at 2, 4, and 12 weeks after discharge. For hospitalizations outside the study center, participants or family members will be asked to provide discharge summaries and key supporting documents (admission/discharge notes, medication records, imaging/laboratory reports). All suspected events will be adjudicated by an independent Clinical Events Committee blinded to treatment allocation and BCM data, using prespecified definitions. Disagreements will be resolved by consensus or a third adjudicator.

After investigators submit the relevant case-report documentation, independent, blinded medical adjudicators contracted for the study will determine 3-month cardiovascular mortality, all-cause mortality, number of heart-failure hospitalizations, time to first heart-failure admission, and any associated questionnaires.

The Kansas City Cardiomyopathy Questionnaire (KCCQ) will be administered at baseline by an independent, blinded assessor on site; at the 3-month follow-up, the same instrument will be completed via telephone by an independent, blinded assessor.

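### As written, the KCCQ mixed model assumes equal variances and one common correlation over three unequally spaced visits, so its 95% confidence intervals may be miscalibrated

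*Protocol article*

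**What the plan says.** The Statistical analysis section of the protocol article covers weight, NT-proBNP and KCCQ together, using "linear mixed-effects models with random participant intercepts" fitted to every measurement at hand. It names no random slope, residual covariance structure or robust standard error.

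The KCCQ outcome, under Study outcomes and measurement, is "the change of Kansas City Cardiomyopathy Questionnaire (KCCQ) quality of life score from baseline to discharge and 3 months after discharge". That makes two contrasts. On timing, the same section says: "Patient-reported quality of life measures will be assessed during hospitalization, at discharge, and at 12 weeks post-discharge". Table 2 places the questionnaire at baseline, discharge and 12 weeks. Under Event ascertainment and adjudication, the baseline questionnaire is given on site, whereas "at the 3-month follow-up, the same instrument will be completed via telephone by an independent, blinded assessor".

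The Study objectives section lists KCCQ among the key secondary endpoints. On status, the Statistical analysis section says: "All secondary endpoints will be analyzed as exploratory; no formal multiplicity adjustment will be applied". For secondary outcomes, "effect estimates with 95% confidence intervals will be reported".

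**The concern.** A random participant intercept with independent residuals is a compound-symmetry model: every visit has the same variance and every pair of visits the same correlation. With complete data it then gives every within-patient change the same standard error, whichever two visits are compared.

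The design gives reasons to doubt this for KCCQ. The first gap is a hospital stay and the second is 12 weeks. Baseline is taken during decompensation, and the other two visits follow treatment. The last visit changes from on-site to telephone administration. Any of these could make the variances or correlations unequal.

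What is at stake is the coverage of two reported intervals. No formal KCCQ test is planned, so the interval is the inference a reader will use.

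**Working it through.** The article states no KCCQ SD, correlation, effect size or power, so it has no KCCQ figure to reproduce. The check is how far the model's standard error can differ from the true one.

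**Inputs from the article.** Three KCCQ visits (Table 2), two contrasts (Study outcomes and measurement), and 242 evaluable patients per group (Sample size). The last only sets the scale of the standard errors; ratios and coverage do not depend on it.

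**Assumptions.** Baseline is one of the modelled responses, means are free by group and visit, and data are complete. Correlations are in the order baseline–discharge / baseline–12 weeks / discharge–12 weeks. SDs are equal unless stated.

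**Formulas.**
- True variance of a change between visits j and k: V_jk = s_j² + s_k² − 2·r_jk·s_j·s_k. With equal SDs this is 2(1 − r_jk)·s².
- Model variance of any change: 2·tr(PΣ)/(3 − 1), with P the centring matrix and Σ the true covariance. With three visits this is the plain average of the three V_jk.
- SE ratio (model/true) = √(model variance / V_jk).
- Coverage of a nominal 95% interval = 2Φ(1.96 × ratio) − 1.

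**Correlations 0.6/0.3/0.4.** In units of s², the true variances are 0.80 (discharge), 1.40 (12 weeks) and 1.20 (discharge to 12 weeks). The average is (0.80 + 1.40 + 1.20)/3 = 1.133.
- Discharge: √(1.133/0.80) = 1.19, coverage about 98.0%.
- 12 weeks: √(1.133/1.40) = 0.90, coverage about 92%.
- Scale, with an assumed SD of 20: the model SE of the between-group difference is √(2 × 1.133 × 400/242) = 1.94 for both contrasts. The true values are √(2 × 0.80 × 400/242) = 1.63 and √(2 × 1.40 × 400/242) = 2.15.

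**Correlations 0.3/0.4/0.6.** The true variances are 1.40, 1.20 and 0.80, and the average is again 1.133.
- Discharge: √(1.133/1.40) = 0.90, coverage about 92%.
- 12 weeks: √(1.133/1.20) = 0.97, coverage about 94%.

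**Range over assumed patterns, equal SDs:**

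| Correlations | SE ratio, discharge | Coverage | SE ratio, 12 weeks | Coverage |
|---|---|---|---|---|
| 0.5/0.5/0.5 | 1.00 | 95.0% | 1.00 | 95.0% |
| 0.6/0.5/0.5 | 1.08 | 96.6% | 0.97 | 94.2% |
| 0.7/0.4/0.5 | 1.25 | 98.6% | 0.88 | 91.6% |
| 0.8/0.3/0.4 | 1.58 | 99.8% | 0.85 | 90.2% |
| 0.5/0.4/0.6 | 1.00 | 95.0% | 0.91 | 92.6% |
| 0.4/0.4/0.6 | 0.94 | 93.5% | 0.94 | 93.5% |

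**Unequal SDs of 20/22/25, correlations 0.7/0.3/0.5.** The true variances are 268, 725 and 559, averaging 517.3. The ratios are √(517.3/268) = 1.39 and √(517.3/725) = 0.84, with coverage about 99.4% and 90.2%.

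So the error can be zero, can affect one contrast or both, and can run in either direction.

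**The case against.** The strongest objection is that the article does not say random intercepts only. A random intercept can be combined with a structured residual covariance or with robust standard errors, and that detail often sits in an analysis plan, which is not shown here. This stands as a limit: the criticism applies to the model as written, under the usual default of independent residuals. It does not remove the point, because the article does choose a model and the choice it names is the one that implies equal correlation.

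A reader might infer that both intervals will be wrong, with the discharge interval too wide and the 12-week interval too narrow. The documents do not support that. It assumes that baseline and discharge are the most strongly correlated pair because they share a hospital stay. The opposite is also plausible: baseline is measured in acute decompensation, while discharge and 12 weeks both follow treatment. Under 0.3/0.4/0.6 both intervals are too narrow, the discharge one more so. Under 0.5/0.4/0.6 the discharge interval is exactly right.

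Two further points stand. The figures assume that baseline is a modelled response. If it enters as a covariate, only two visits are modelled and these ratios do not apply as given. Also, the endpoint is exploratory, its estimates are to be read with caution, and mild departures cost little (94.2% and 96.6% under 0.6/0.5/0.5).

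**Conclusion.** The point holds in conditional form. The stated model, with independent residuals, assumes equal variances and one correlation over visits whose spacing and mode of administration make that doubtful. The 95% intervals for the two KCCQ changes may therefore be miscalibrated. Under the assumed patterns, coverage ran from 90.2% to 94.2% where an interval was too narrow and from 96.6% to 99.8% where it was too wide. It was exactly 95% where all correlations and SDs were equal. Direction and size cannot be settled from the documents, because every correlation and SD used here is an assumption.

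It would also go too far to infer that the KCCQ treatment effect itself is biased. With complete data and means free by group and visit, the point estimates are the same under either covariance. Missing visits would bring the covariance into the weighting of the estimates as well. The primary endpoint uses a different analysis and is untouched. This is a small improvement, not a threat to the trial's conclusion.

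**What to change.** For KCCQ, replace the random-intercept wording with a repeated-measures mixed model that has visit as a category, group-by-visit terms and an unstructured covariance over the visits. State whether baseline is a response or a covariate. Report the discharge and 12-week contrasts from this model with their 95% confidence intervals.

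The cost is one sentence, with no extra data or patients. With baseline as a response, three visits need six covariance parameters (three variances and three correlations). That is immaterial with about 500 patients (2 × 242 = 484 evaluable, 538 targeted). Both named packages, SPSS and R, can fit it. If variances and correlations turn out to be equal, essentially nothing is lost. The change should be made before the data are analysed.
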